## **4.8 Data Analysis**

### **4.8.1 Quantitative Data Analysis**

Quantitative data analysis will be done and will consist of univariate and multivariate logistic regression analysis. Stata version 13.1 will be used for this analysis. The ITM Principal Investigator (PI) and statistician will be responsible for carrying out the data analysis.

The predictors for mortality that will be analyzed are indicated under section 4.7.1. The main outcome measured is in-health center/hospital mortality. The aim of the analysis is to identify independent predictors for mortality. These independent predictors of mortality shall be used to develop a clinical prediction score as explained below under section 4.8.2.

### **4.8.2 Score Building**

The score will be developed using the Spiegelhalter and Knill-Jones method. Derivation of the clinical prediction score will be done in the 2008-2013 data. Five-fold cross validation and external validation will be performed. The procedure of building the score is as outlined below.

- Crude likelihood ratios (LHR) will be calculated for all variables and those with a LHR  $\geq 2$  or  $\leq 0.5$  will be selected for inclusion in the score building.
- To adjust for correlations between predictors, LHR will be adjusted using multivariate logistic regression.
- Variables independently associated with mortality with a LHR  $\geq 1.5$  or  $\leq 0.67$  will be retained.

- To develop the scoring system, the predictor score for each predictor will be obtained by calculating the natural logarithm of the adjusted LHR and rounding this result to the nearest integer.
- Summing the predictor scores of the individual's risk factors will yield the total predictor score for each patient.
- The performance of the clinical prediction score using the validation dataset will be evaluated by calculating the sensitivity, specificity, positive predictive value, negative predictive value, LHR at different cut offs; its overall performance will be assessed using the area under the receiver operating characteristic curve and 95% CI.
- Based on these data, different risk groups can be identified using different cut-offs (e.g. low, intermediate and high risk groups).

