## **Statistical methods**

Statistical analysis will be done with Stata version 13.1. The main exposure variables in 10% of the patient charts will be validated against the records in the excel database. Univariate and multivariate logistic regression analysis will be done. The Spiegelhalter and Knill Jones method will be used to develop the score. Predictors with an adjusted likelihood ratio of  $\leq 0.67$  and  $\geq 1.5$  will be used to develop the score. A receiver operating characteristic curve will be constructed and cut off selected with the Zweig and Campbell formula.

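### Section 4.8.2 retains predictors at adjusted LHR 1.5 or 0.67, but its rounding rule gives 0 points to any retained category below about 1.65 or above about 0.607

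*Protocol*

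**What the plan says.** Section 4.8.2 (Score Building) sets out a sequence of steps.

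- A crude screen keeps variables with an LHR of at least 2 or at most 0.5.
- The LHRs are then adjusted for correlation between predictors by multivariate logistic regression.
- The retention step begins "Variables independently associated with mortality with a LHR" and sets the limits at 1.5 or above, or 0.67 or below.
- The points for each predictor are "obtained by calculating the natural logarithm of the adjusted LHR and rounding this result to the nearest integer".
- The total is a plain sum: "Summing the predictor scores of the individual's risk factors will yield the total predictor score for each patient".

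The Summary (Statistical methods) repeats the retention limits in a sentence that begins "Predictors with an adjusted likelihood ratio of" and assigns the predictors meeting them to building the score.

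Section 4.3 limits the final model to 9 parameters for all VL patients (99 deaths) and 5 for VL-HIV patients (51 deaths). The protocol gives no scaling factor before rounding, no minimum of one point, and no rule for a retained predictor whose points come to zero.

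**The concern.** The retention limits and the scoring unit were set on different scales. Retention works at about 0.4 on the log scale, while a point is earned only from 0.5. Between the two lies a band in which a predictor is declared independent and kept, yet contributes nothing to any patient's total.

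The integer score is the study's primary product, and its AUC is to be judged against 0.75 (section 3.1). A zero-point category can be listed as part of the score without affecting it, and it can use a parameter that section 4.3 rations. This matters most in the VL-HIV model, where only five are allowed. The same coarse unit also treats a weak and a fairly strong predictor alike: LHR 1.7 and LHR 4.4 both score 1.

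**Working it through.** **Inputs.** Retention limits 1.5 and 0.67, crude limits 2 and 0.5, and points = round(ln adjusted LHR), all from section 4.8.2. Parameter limits 9 and 5 from section 4.3. The protocol states no figure for the effect of rounding, so there is none to reproduce.

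**Step 1: points at the plan's own limits.** ln(1.5) = 0.405, which rounds to 0. ln(0.67) = -0.400, which rounds to 0.

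**Step 2: where points begin.** Rounding changes at half-units:

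- exp(0.5) = 1.649 for +1
- exp(1.5) = 4.482 for +2
- exp(-0.5) = 0.607 for -1
- exp(-1.5) = 0.223 for -2

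| Adjusted LHR | ln | Points as written | Points with 2 x ln |
|---|---|---|---|
| 0.50 | -0.693 | -1 | -1 |
| 0.60 | -0.511 | -1 | -1 |
| 0.61 | -0.494 | 0 | -1 |
| 0.67 | -0.400 | 0 | -1 |
| 1.50 | 0.405 | 0 | 1 |
| 1.64 | 0.495 | 0 | 1 |
| 1.65 | 0.501 | 1 | 1 |
| 3.00 | 1.099 | 1 | 2 |
| 4.48 | 1.4996 | 1 | 3 |

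Retained categories that score 0 are those at 1.50-1.649 and 0.607-0.67. The one-point band runs from 1.65 to 4.48, a ratio of 4.48/1.65 = 2.7.

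**Step 3: can the zero band be reached?** A variable entering at the crude limit has ln(2) = 0.693, which would round to 1. It falls into the zero band if adjustment leaves between 0.405/0.693 = 58% and 0.5/0.693 = 72% of its log LHR. Adjustment is there to account for correlated predictors, and a retention limit below the crude limit makes sense only if such shrinkage is expected. So the band is reachable.

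**Step 4: size under assumed inputs.** The AUC loss cannot be computed from the protocol. The following simulations rest on assumptions: 16 binary candidates, 10 of them predictive, cohorts of n = 1729 and n = 345, and 200 datasets per scenario.

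- *Latent correlation 0.2-0.4, first set of effects.* True AUC, unrounded against integer: 0.801 vs 0.784, 0.821 vs 0.800 and 0.808 vs 0.794 (all VL); 0.784 vs 0.770, 0.822 vs 0.806 and 0.844 vs 0.830 (VL-HIV). Differences are 0.014 to 0.021. At least one retained predictor scored 0 in 60-79% of datasets.
- *Latent correlation 0.2-0.4, second set (log-odds 0.2-1.4, prevalence 5-50%).* 0.851 vs 0.835 and 0.902 vs 0.889 (n = 1729); 0.816 vs 0.803 and 0.866 vs 0.851 (n = 345). Differences are 0.013 to 0.016. Doubling before rounding gave 0.849, 0.901, 0.814 and 0.865, within 0.001-0.002 of unrounded.
- *Uncorrelated predictors.* The loss was 0.001-0.003.
- *Parameter limits applied (a separate simulation, assumed effects, correlation 0.3).* Keeping the five strongest predictors in VL-HIV cut the share of datasets with a zero-point predictor from 76% to 25%, and the loss from 0.018 to 0.010. In all VL, the limit of nine changed the loss only from 0.026 to 0.021.

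**The case against.** The strongest reply is that integer rounding is deliberate. Section 1.2 asks for easy-to-use tools, and a score made mostly of one-point items is close to a checklist count. That stands for the 1.65-4.48 band, which is partly the ordinary price of a simple score. It does not explain the zero band, because doubling before rounding also gives integers.

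A reader might infer that the two rules contradict each other so that the plan cannot be run. It can. The steps execute in sequence, and the effect is that the working limits for earning a point become about 1.65 and 0.607. The affected band is narrow, about 0.1 log unit on each side.

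A reader might also infer that a retained variable in the band can never move the score. An LHR belongs to a category. A variable with 1.6 for one level and 0.5 for another scores 0 and -1, so it still contributes. Several candidates in section 4.7.1 are not binary, and section 4.7.2 gives weakness three levels. Section 4.8.2 speaks of an individual's risk factors, which may mean that only presence is scored, but it does not settle this.

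The AUC loss is also small beside sampling error. At AUC 0.80 the Hanley-McNeil standard error is about 0.027 (99 deaths, 1630 survivors), 0.037 (53 and 473) and 0.060 (28 and 27). Nor is the reported performance biased: the score evaluated is the integer score itself, so any loss shows in its AUC.

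The point could be left to a statistical analysis plan only if the protocol were silent. It fixes both rules.

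**Conclusion.** The mismatch is real and follows from the protocol's own figures. A retained category with adjusted LHR 1.50-1.649 or 0.607-0.67 receives no points, contrary to the use the Summary gives it, and may take one of the 9 or 5 permitted parameters. No other section resolves this.

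The consequence for discrimination is modest and depends on assumptions: about 0.001-0.003 in AUC with uncorrelated predictors, up to about 0.02 with correlated ones, and smaller in VL-HIV under the 5-parameter cap (0.010 in the one simulation that applied it). A reader might conclude that rounding would make the study miss its 0.75 target. Nothing supports that: every simulated integer score listed above exceeds 0.75 (lowest 0.770), and the protocol gives no estimates from which to predict the real value.

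This should be fixed before analysis, mainly because a remedy chosen after the LHRs are known would be driven by the data. It does not threaten the validity of the study.

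**What to change.** State in section 4.8.2, before analysis, that points equal 2 x ln(adjusted LHR) rounded to the nearest integer, and that the factor 2 is fixed and not chosen from the data. Then 1.5 scores 1 (2 x 0.405 = 0.81), 0.67 scores -1 (2 x -0.400 = -0.80) and 4.48 scores 3 (2 x 1.4996 = 3.00). Every retained category scores, because the first point is earned from exp(0.25) = 1.28 upwards or exp(-0.25) = 0.78 downwards. Report the AUC of the unrounded score beside that of the integer score, so that the cost of rounding is visible.

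If one point per log unit is preferred, change the retention limits in both section 4.8.2 and the Summary to at least 1.65 and at most 0.60. A lower limit of 0.61 would not work, since ln(0.61) = -0.494 still rounds to 0.

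The cost of the main change is a sentence or two and slightly larger point values to add up at the bedside. No new data are needed.

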### Sample Size

1. Development of the score:

All VL patients: VL patients diagnosed between January 2008 to December 2013. There were 1729 patients diagnosed in this period among whom 99 died.

VL-HIV co-infected patients. VL patients diagnosed between January 2008 to December 2013. There were 345 patients diagnosed in this period among whom 51 died.

2. External validation:

All VL patients: VL patients diagnosed between January 2011 to December 2012. There were 526 patients diagnosed in this period among whom 53 died.

VL-HIV co-infected patients. VL patients diagnosed between January 2011 to December 2012. There were 55 patients diagnosed in this period among whom 28 died.

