## 4. METHODS

### 4.1 Study Setting

**Development of the tool** will be conducted in Abdurafi Health centre in Abdurafi town, West-Armacheo district, North West Ethiopia. It is a poor and remote district with poor access to health. It has one of the highest burden of VL and HIV in Ethiopia. Seasonal crop farming is one of the main activities and approximately 300,000 migrant workers travel in and out of the region seasonally. Commercial sex work is also very common.

The health centre belongs to the Ethiopian bureau of health and has been supported by Médecins Sans Frontières Holland (MSFH) since 2004. It focusses on the clinical management of VL, HIV and concomitant infections. It is one of the main VL treatment sites in Ethiopia and medical services are free of charge. The majority of the patients treated are migrant workers.

We consider this site suitable for our study because of the following facts:

- (1) Ethiopia is one of the top six countries in the world with the highest burden of VL and it has the highest burden of VL-HIV Co-infection.
- (2) Readily available high quality data: Since the VL program onset in 2004, standardized data collection sheets (patient cards) have been used, from which data are transferred to an electronic database. (See Annex 1) Clinical teams are trained on standardized clinical procedures and data collection and a data quality system is in place.
- (3) The VL mortality rate remains high in the health center.

**External validation of the tool** will be conducted at the Leishmania Research and Treatment Center (LRTC) at the University of Gondar Hospital supported by the Drugs for Neglected Diseases Initiative (DNDi). The LRTC is located in Gondar city and is the main referral facility for critically ill or complicated VL cases. The main focus for this centre, is the clinical management of VL and concomitant infections and clinical research on VL. It is one of the main VL treatment sites in the high HIV co-infection burden area and medical services are free of charge. We consider this site suitable because along with Abdurafi health centre they are the main VL treatment sites in the high HIV co-infection burden area. Furthermore there is readily available high quality data collected using standardized data collection forms.

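### Section 4.8.2 appears to set the risk-group cut-offs from the validation results, and no step fixes them in the derivation data first

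*Protocol*

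**What the plan says.** Section 4.8.2 (Score Building) derives the score in the 2008-2013 data and announces both five-fold cross-validation and external validation. Its last two steps are:

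- "The performance of the clinical prediction score using the validation dataset will be evaluated", by sensitivity, specificity, predictive values and likelihood ratio (LHR) at different cut-offs, with the AUC and its 95% CI as the overall measure.
- "Based on these data, different risk groups can be identified using different cut-offs", with low, intermediate and high risk given as examples.

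The Summary (Statistical methods) has a further rule that section 4.8.2 does not mention: a ROC curve is drawn and the "cut off selected with the Zweig and Campbell formula". It does not say in which cohort.

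Section 1.2 promises a score that is developed and externally validated. Section 3.4 and the Summary (Main results) list algorithms defining groups with differing mortality risk as outputs. Section 4.1 describes the external validation site, the LRTC, as the "main referral facility for critically ill or complicated VL cases".

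**The concern.** External validation tests a rule that was fixed beforehand. If the boundaries between risk groups are picked after seeing which ones work well in the validation cohort, that cohort no longer tests them. The score would still be externally validated, but the risk groups would not, and the groups are what a clinician would use.

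Three consequences follow:

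- Sensitivity and specificity at a cut-off singled out this way are biased upwards.
- The cut-off itself can depend on the cohort, because the Zweig and Campbell formula includes the prevalence of the outcome, and mortality differs markedly between the two sites.
- A good AUC can coexist with wrong absolute risks per group. The listed measures (AUC, sensitivity, specificity, predictive values, LHR) do not compare predicted with observed mortality. The Summary (Impact) and section 1.2 foresee using the tool to decide who is treated in hospital and who in a health centre, where absolute risk matters.

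**Working it through.** **Inputs** (Summary, Sample Size). All VL, derivation: "There were 1729 patients diagnosed in this period among whom 99 died". VL-HIV, derivation: "There were 345 patients diagnosed in this period among whom 51 died". All VL, validation: "There were 526 patients diagnosed in this period among whom 53 died". VL-HIV, validation: "There were 55 patients diagnosed in this period among whom 28 died".

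**The plan's own figure.** The Protocol calculates nothing on cut-offs. Its one derived figure, the parameter limit in section 4.3, reproduces: 99/10 = 9.9, so 9; 51/10 = 5.1, so 5.

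**Step 1: mortality by cohort.** Risk = deaths/patients. The 95% CI of the ratio is Wald on the log scale, with SE = √(1/d₁ − 1/n₁ + 1/d₂ − 1/n₂).

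| Population | Derivation | Validation | Ratio (95% CI) |
|---|---|---|---|
| All VL | 99/1729 = 5.73% | 53/526 = 10.08% | 1.76 (1.28 to 2.42) |
| VL-HIV | 51/345 = 14.78% | 28/55 = 50.91% | 3.44 (2.40 to 4.95) |

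If the VL-HIV counts are nested in the totals, the remaining patients have 48/1384 = 3.5% against 25/471 = 5.3%, a ratio of 1.5.

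**Step 2: effect on a Zweig and Campbell cut-off.** The formula picks the ROC point where the slope equals (cost of a false positive / cost of a false negative) × (1 − p)/p. The prevalence term (1 − p)/p is:

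| Population | Derivation | Validation | Derivation / validation |
|---|---|---|---|
| All VL | 1630/99 = 16.5 | 473/53 = 8.9 | 1.84 |
| VL-HIV | 294/51 = 5.8 | 27/28 = 0.96 | 5.98 |

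The Protocol gives no cost ratio, so the slopes themselves are not fixed. If a missed death were weighted 10 times a false alarm (an assumption), they would be 1.65 against 0.89 and 0.58 against 0.10. The last column does not depend on the cost ratio, since it cancels. With any common cost ratio, the formula can therefore choose a different cut-off in each cohort.

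**Step 3: effect on predictive values.** Post-test risk = prior odds × LHR / (1 + prior odds × LHR). The LHR values are illustrative:

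| LHR | All VL, derivation | All VL, validation | VL-HIV, derivation | VL-HIV, validation |
|---|---|---|---|---|
| 0.2 | 1.2% | 2.2% | 3.4% | 17.2% |
| 0.5 | 2.9% | 5.3% | 8.0% | 34.1% |
| 2 | 10.8% | 18.3% | 25.8% | 67.5% |
| 5 | 23.3% | 35.9% | 46.4% | 83.8% |

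The same score result carries a different risk at each site.

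**Step 4: optimism from choosing a cut-off in the validation set.** Simulation with 4,000 replicates. Assumptions: binormal score rounded to integers, one cut-off chosen by maximum Youden index (sensitivity + specificity − 1). The Protocol does not state this selection rule.

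| Validation cohort | True AUC | Apparent index | True index at that cut-off | Optimism |
|---|---|---|---|---|
| All VL, 53 deaths | 0.75 | 0.380 | 0.350 | 0.030 |
| All VL, 53 deaths | 0.80 | 0.461 | 0.432 | 0.028 |
| VL-HIV, 28 deaths | 0.75 | 0.411 | 0.334 | 0.077 |
| VL-HIV, 28 deaths | 0.80 | 0.487 | 0.418 | 0.069 |

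**The case against.** The strongest reply is that the text leaves the matter open and states no wrong rule. The term validation dataset is not defined. Section 4.8.2 names two validations, and section 4.3 assigns five-fold cross-validation in the development patients to evaluating the score's performance. The wording on risk groups is also permissive. This stands in part. If the cross-validation folds were meant, the cut-offs would come from derivation data, close to the remedy below, and the contrast between sites would not bear on how they are chosen. But section 4.8.2 would then list no outputs for the external validation, so the external cohort is the likelier reading. The wording needs correcting either way.

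A table of accuracy across all score values carries no selection optimism; only singling out cut-offs from it does. That is right, and it limits the harm to the risk groups and any chosen cut-off. Reporting the LHR also lets a user convert to the local mortality.

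Readers might infer more than the documents support:

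- That LRTC mortality will be quoted for health centres. No section says so.
- That the Summary and section 4.8.2 contradict each other. One optimal cut-off and several risk strata can coexist; the fault is that neither place names the cohort for the formula.
- That at a slope of 16.5 only patients with at least 50% risk would be flagged. That threshold follows from equal costs alone, at any prevalence. With a 10-to-1 weighting it is 1/11, about 9%.
- That the missing cost ratio or calibration statistics are defects in themselves. An SAP that is not shown may hold them.

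**Conclusion.** The concern holds as a point that should be fixed, not as one that undermines the study. On its most natural reading, section 4.8.2 lets the risk groups be chosen from the validation results. Groups chosen that way could not be called externally validated. The primary objective, an AUC above 0.75, uses no cut-off and is unaffected, as are score derivation and predictor selection.

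The optimism in sensitivity + specificity − 1 is modest for all VL (about 0.03) and larger for VL-HIV (0.07 to 0.08), a tertiary objective. Both figures depend on the assumed maximum-Youden selection and binormal score. The firmer figures are the mortality ratios, 1.76 and 3.44, which come straight from the Protocol's counts and make predictive values and any prevalence-dependent cut-off specific to the cohort. Two caveats apply: the VL-HIV ratio rests on 55 validation patients, and the Protocol does not say whether the 526 and 55 are counted before or after exclusions, so the ratios could shift somewhat.

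**What to change.** In section 4.8.2:

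1. State that cut-offs and risk groups are set in the 2008-2013 derivation data, using cross-validated scores, then locked and applied unchanged to the LRTC cohort.
2. Define the validation dataset, and say which outputs come from cross-validation and which from the external cohort.
3. Add to the external validation outputs the mortality predicted from the derivation data against the mortality observed at the LRTC, per risk group.
4. Give the same cut-off method and cohort here and in the Summary. If the Zweig and Campbell formula is kept, say which prevalence it uses.

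Optional, and suitable for the SAP: the cost ratio, fixed before the analysis; calibration intercept and slope; and predictive values at both cohorts' mortality.

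The cost is Protocol wording and a little more analysis, with no new data. The validated sensitivity and specificity may come out slightly less favourable.

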## **5. ETHICAL ISSUES**

### **5.1 Ethical (and Regulatory) Review**

This protocol and any subsequent amendments will be submitted for approval to the Institutional Review Board of the ITM, the MSFH Ethics Committee and the Ethical Review Board of the Institute of Public Health, Gondar University. The study will be carried out according to the principles stated in the Declaration of Helsinki, all applicable regulations and according to established international scientific standards. Ethical approval for use of retrospective data from LRTC was obtained from University of Gondar IRB.

### **5.2 Risks and Benefits**

This study is observational and not experimental. It consists of retrospective analysis of anonymized routinely collected program data. There is no direct risk for the patients. The final results of the study will be beneficial for better clinical management of patients. All patients are treated following the national, MSFH guidelines and latest scientific evidences.

